#### *CRP&SAA POCT*

Serum Amyloid A/C-Reactive Protein Combined Assay Kit (Immunochromatography) will be supplied to all village clinics in the intervention arm for the target population (ARIs patients). Since the purpose of this study is to determine whether antibiotic prescribing for ARIs can be guided by the use of CRP&SAA POCT, the intervention arm should be encouraged to utilise CRP&SAA POCT for all target populations (patients with ARIs). This recommendation is suggested but not mandated. The control arm will not receive any intervention (usual care). Village doctors will decide whether to prescribe antibiotics to patients with ARIs based on the recommended threshold for CRP&SAA levels (mg/L). As there is currently no specific cut-off threshold for CRP and SAA, our recommended threshold was developed in conjunction with previous studies and expert consensus in China to align more closely with clinical practice. In order to further encourage village doctors to utilise CRP&SAA POCT, we simulated real-world conditions. According to the reimbursement policy, the Rural Cooperative Medical Care in China, provides a 60% reimbursement for visits to village clinics. Each patient with an ARI utilizing the CPR&SAA POCT, originally priced at 14 yuan (approximately US \$1.92), will ultimately pay 5 yuan (approximately US \$0.68) to the village clinic.

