#### *Patient education*

For the village clinics in the intervention arm, patients presenting with ARIs will receive a popular science leaflet detailing the role of CRP&SAA POCT in promoting the rational use of antibiotics for ARIs, as well as the risks associated with antibiotic overuse. According to the information provided in the publicity leaflet and the advice of the village doctor, patients with ARIs (or their legally appointed agents) will determine whether to consent to CRP&SAA POCT based on their individual circumstances.

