#### **Usual care**

Village clinics in the control arm will continue to prescribe antibiotics to patients with ARIs in accordance with the current national guidelines and usual care in village clinics. In usual care, village doctor will diagnose and treatment of ARIs based on their clinical experience and existing knowledge, and make decision on whether to prescribe antibiotics. Notably, the village doctors in the control arm will not receive any education on ARIs and the appropriate use of antibiotics, and will not receive the Serum Amyloid A/C-Reactive Protein Combined Assay Kit.

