#### **Allocation and blinding**

The 40 village clinics will be randomly assigned to one of the two arms, stratified by township, to prevent any imbalance in distribution among townships, while considering potentially significant variation in outcomes between townships. Randomisation will be conducted using R version 4.0.5 (R Foundation for Statistical Computing). ARIs patients and village doctors will not be blinded to the treatment; however, measures will be implemented to ensure a blinded outcome evaluation by employing the 'PROBE' design.

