### **Sample size**

Based on our exploratory study and previous research, the antibiotic prescription rate in rural primary healthcare institutions in China ranges from 50% to 80%. The minimum value of 50% is utilised as a conservative estimate of the conventional antibiotic prescription rate in the control arms. We conservatively estimate that CRP&SAA POCT intervention will lead to at least a 25% relative reduction in the antibiotic prescription rate in village clinics. Thus, to detect a reduction of 25% or more in the antibiotic prescription rate - specifically, an absolute reduction to 37.5% antibiotic prescription rate or lower - with 90% power, utilizing two-sided testing at the 5% significant level, and assuming a harmonic mean cluster size of 500 along with an intracluster correlation coefficient of 0.05, we estimate that we will require 17 village clinics per arm. Allowing for a 15% loss of prescription data and considering that 20 village clinics are required per arm, it was decided to include a total of 40 village clinics.

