### **Data analysis plan**

All analyses will be conducted on the intention-to-treat (ITT) population, defined as all outpatient prescriptions issued by village clinics for ARI patients, regardless of the compliance of village doctors and patients with the intervention. For the primary and secondary outcomes, which are binary variables, we will employ Generalised estimating equations (GEEs) to estimate both relative and absolute measures of effect. The same methods will be used to analyse the mean cost of an ARI prescription and a consultation. The primary outcome will also be analysed in subgroups based on ARI

patient's age (1-15 / 16-65 / over 65 years old), ARI patient's sex (male / female), type of ARI (upper respiratory tract infection / lower respiratory tract infection), and season. Likelihood ratio tests will be employed to assess the heterogeneity of antibiotic prescribing across these different subgroups. We also will conduct per-protocol analyses, which included only ARI patients who received CRP&SAA POCT in village clinics within the intervention arm. Furthermore, modified poisson regression and linear regression models, which account for village-level clustering using the clustered sandwich estimator, will be employed to replicate all results and assess their robustness. No interim analyses are planned, and all outcomes will be analysed following data collection.

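### The per-protocol set keeps only intervention patients who were tested; any comparison of it with control is not randomised and can be biased in either direction

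*Protocol*

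**What the plan says.** Protocol, Data analysis plan, opens by assigning every analysis to the ITT population, which is "defined as all outpatient prescriptions issued by village clinics for ARI patients, regardless of the compliance of village doctors and patients with the intervention". The same section then adds "per-protocol analyses, which included only ARI patients who received CRP&SAA POCT in village clinics within the intervention arm". It names no comparator for that set and gives no adjustment, weighting or caveat for it. It also plans to replicate all results with modified Poisson and linear regression using a clustered sandwich estimator.

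Three other sections determine who ends up in the tested set:

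- **CRP&SAA POCT.** Intervention clinics are encouraged to test every patient with an acute respiratory infection (ARI), but "This recommendation is suggested but not mandated". The patient pays 5 yuan for the test.
- **Patient education.** After a leaflet and the doctor's advice, patients or their agents "will determine whether to consent to CRP&SAA POCT based on their individual circumstances".
- **Usual care.** Control doctors "will not receive the Serum Amyloid A/C-Reactive Protein Combined Assay Kit".

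Under Allocation and blinding, "ARIs patients and village doctors will not be blinded to the treatment".

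**The concern.** Membership of the per-protocol set depends on a choice made after randomisation. The doctor who helps make that choice also writes the prescription, which is the outcome, and knows the arm. If testing is related to the doctor's prior inclination to prescribe, or to what the patient expects, tested patients differ from the whole clinic population before the test result has had any influence. The control arm cannot be cut down to its would-be-tested patients, because nobody there is offered the test.

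At stake is how a second, apparently supportive estimate would be read. A tested-only result more favourable than the ITT result could be taken as the effect of the test when it is used, and a less favourable one as evidence that testing does little. Either could come from selection alone. The planned replication with other regression models would not reveal this, since refitting the same selected patients reproduces the same bias.

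**Working it through.** **Inputs from the protocol (Sample size).** "The minimum value of 50% is utilised as a conservative estimate of the conventional antibiotic prescription rate in the control arms". A 25% relative reduction gives 0.50 × 0.75 = 0.375, so the planned effect is 12.5 points. The design assumes a cluster size of 500, an intracluster correlation of 0.05, 90% power and a two-sided 5% level.

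**The plan's own figure.** The individually randomised size for 50% versus 37.5% is 329 per arm (325.73 with unpooled variance). The design effect is 1 + 499 × 0.05 = 25.95. Then 329 × 25.95 / 500 = 17.08 clinics per arm (16.91 unpooled). Power at 17 clinics is 89.9%, and 17 / 0.85 = 20. The stated 17 and 20 reproduce, so no printed number is in dispute.

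**Inputs the protocol does not give (assumed).** Uptake u is set at 40%, 60% and 80%. The gap g is the untested rate minus the tested rate that would hold without any effect, set at ±10 and ±20 points.

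**Shift in the tested-only rate with no true effect.** The overall rate is P = u × pT + (1 − u) × pU, with pU = pT + g. Hence pT = P − (1 − u) × g. With P = 50%:

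| Uptake | g = +20 | g = +10 | g = −10 | g = −20 |
|---|---|---|---|---|
| 40% | 38% (−12) | 44% (−6) | 56% (+6) | 62% (+12) |
| 60% | 42% (−8) | 46% (−4) | 54% (+4) | 58% (+8) |
| 80% | 46% (−4) | 48% (−2) | 52% (+2) | 54% (+4) |

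The control rate is 50% throughout, so the bracketed figures are pure selection.

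**How a real benefit can be hidden.** Suppose testing truly lowers prescribing in tested patients by 12.5 points, with u = 40% and g = −20. The tested-only rate is 62 − 12.5 = 49.5%, against 50% in control: an apparent reduction of 0.5 points.

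**Error rate when there is no effect.** A simulation used 20 clinics per arm, 500 patients per clinic, beta-binomial clustering with correlation 0.05, a true 50% rate in both arms, and 4,000 runs per setting. A cluster-level t-test stood in for the planned generalised estimating equations. Selection was set by r, the probability of being tested among patients who would not receive antibiotics divided by that among patients who would. At a 50% rate the expected tested-only rate is 1 / (1 + r), whatever the uptake. Uptake of 50% and 70% was run.

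| r (assumed) | Tested-only rate | Ratio to control | Tested-only rejections at 5% |
|---|---|---|---|
| 1 | 50.0% | 1.00 | about 5% |
| 1.25 | 44.4% | 0.89 | about 30% |
| 1.5 | 40.0% | 0.80 | 72% to 74% |
| 2 | 33.3% | 0.67 | above 99% |

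The ITT comparison rejected in 4.8% to 6.1% of runs in every setting.

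The two parameterisations agree. At 50% uptake, r = 1.5 gives tested and untested rates of 40% and 60%, so g = 20 and (1 − 0.5) × 20 = 10 points. The case r = 2 is stronger than the first table allows: at 50% uptake it implies rates of 33.3% and 66.7%, a gap of about 33 points. Values of r below 1 were not simulated, but the formula shows the reversal: r = 0.8 gives 1 / 1.8 = 55.6%, a ratio of 1.11.

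**The case against.** The strongest reply is that nothing important depends on this analysis. ITT is the main analysis, the per-protocol analysis is an addition, and neither the sample size nor any decision rule uses it. The primary outcome is described as reflecting the comprehensive intervention as a whole, not the effect of being tested. All of this stands and limits the weight of the point. A reader might infer that the trial's main conclusion is compromised; the protocol does not support that.

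A second reply is that the comparator, any adjustment and the interpretive caveats could be in a statistical analysis plan that is not at hand. This stands in part. The protocol does not say that tested patients are compared with all controls; that is an inference, though the natural one. What the protocol does fix is the restriction to tested patients, and a plan that follows it inherits the selection.

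Third, it is tempting to conclude that the analysis will favour the intervention, because doctors already set on prescribing would skip the test. The documents do not show this. A doctor certain that a mild cold needs no antibiotic may also skip it, and a mildly ill patient may decline to pay. The direction is unknown.

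Fourth, uptake may be high. The training, the week of on-site guidance and the monthly feedback are meant to support use of the test, and at 80% uptake the shift is only 2 to 4 points. This is fair, but uptake is not known in advance.

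Finally, every per-protocol analysis gives up some of the protection of randomisation. What is particular here is that the restriction can be applied in one arm only.

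**Conclusion.** The point holds for a supplementary analysis. Followed exactly, the protocol defines a subset selected after randomisation with no counterpart in control, so a contrast with control patients does not estimate the effect of the intervention or of testing without further assumptions, and the protocol states none.

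Under the assumed uptake and gaps, the distortion runs from 2 to 12 points in either direction. The 12-point end needs both the lowest uptake and the widest gap considered. The rejection rates in the simulation likewise rest on assumed values of r. These figures show what selection could do; they do not predict what it will do in this trial.

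The section also contradicts itself, assigning all analyses to the ITT population and then adding one that is not. The matter is worth correcting before analysis, but it does not threaten the primary result.

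**What to change.** 1. In Data analysis plan, do not present the tested-only versus control contrast as a treatment effect. Report uptake in intervention clinics, and prescribing among tested and untested intervention patients, as descriptive data labelled non-randomised and exploratory. This serves the fidelity objective already stated under Process evaluation.
2. Reword the opening sentence of that section so that it no longer assigns every analysis to the ITT population while another population is used; for example, limit it to the primary and secondary effect estimates.
3. Optionally, if an estimate of the effect of use is wanted, add a complier-average estimate as a sensitivity analysis, with randomised arm as the instrument and clustering by clinic. Non-compliance is one-sided, because control clinics are not given the kit. State that the exclusion restriction is doubtful: training, leaflets and feedback also reach untested patients, so the estimate overstates the effect of testing if those components also reduce prescribing. For that reason it should not become the replacement headline.

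The cost is wording and, if the optional model is used, one further model on data already collected. The downside is the loss of a conventional per-protocol effect estimate, and a wider interval from the optional model.

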**Methods****Design**

This is a pragmatic, parallel-group, cluster randomised controlled trial designed to evaluate the impact of a CRP&SAA POCT-based comprehensive intervention on

antibiotic prescribing for patients with ARIs in Chinese village clinics. This study will be conducted over a period of six months across 40 village clinics, with randomization stratified by township. CRP&SAA POCT will be implemented in 20 village clinics within the intervention arm. This will include additional training for village doctors on the operations of CRP&SAA POCT, which encompasses centralised training, the distribution of training manuals, and desk reminders. The aim is to help village doctors understand the significance of CRP&SAA POCT in guiding antibiotic prescriptions and to familiarise them with the specific operational procedures. Additionally, patient education materials will be provided to assist patients in understanding how CRP&SAA POCT can aid in their diagnosis and treatment. The control arm will not receive any intervention and will continue with usual care.

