### **Setting**

As the primary providers of health care services in rural China, village clinics address various aspects, including basic medical services, preventive health care, public health services, and drug supply, with the goal of meeting the fundamental medical and public health needs of rural residents. This study will be conducted in 40 village clinics across 15 townships and 4 sub-district offices (equivalent to townships) in Xiantao, Hubei Province. Xiantao is situated in central China's Hubei Province, with a population of approximately 1.11 million permanent residents. The city administers 15 townships and 4 sub-district offices. Each village clinic employs 1 to 2 upgraded community health workers, commonly referred to as 'village doctors'. All village doctors have successfully passed the national doctor qualification examination and have obtained either a certificate of practicing physician qualification or a certificate of practicing assistant physician qualification. This includes qualifications for practicing as a physician or assistant physician in the clinical category, as well as the rural general practice assistant physician qualification.

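### Clinics are randomised within 19 townships, about two in each, but the stated analysis contains no township term

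*Protocol*

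**What the plan says.** Under Allocation and blinding, the protocol states that "The 40 village clinics will be randomly assigned to one of the two arms, stratified by township", and gives as part of the reason "while considering potentially significant variation in outcomes between townships". Setting places the trial in "40 village clinics across 15 townships and 4 sub-district offices", the latter being treated as townships. That makes 15 + 4 = 19 strata and 40/19 = 2.1 clinics per stratum on average. The actual number of clinics in each township is not given. Design allocates 20 clinics to each arm.

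The Data analysis plan says of the primary and secondary binary outcomes that "we will employ Generalised estimating equations (GEEs) to estimate both relative and absolute measures of effect". For the GEE it gives no cluster unit, covariates, variance estimator or reference distribution. It then adds modified Poisson and linear models that "account for village-level clustering using the clustered sandwich estimator", as a robustness check. Township does not appear in that section.

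**The concern.** Stratifying by township balances the arms within townships, so differences between townships drop out of the true error of the treatment comparison. An analysis without township still counts those differences in its estimated standard error. Intervals then come out too wide and the test too cautious, the more so the more townships differ. The protocol's own reason for stratifying is that they may differ.

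A second effect works the other way. An uncorrected sandwich variance with 40 clusters is slightly too small and makes the test mildly liberal. The net result depends on how much townships vary.

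At stake are the calibration of the primary interval and p-value, and part of the precision that stratification was meant to buy. There is also a trap for whoever adds township later: the obvious patch, township indicators with the village-level sandwich that the protocol already names, is badly anti-conservative.

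**Working it through.** **The protocol's own figure.** Inputs from Sample size: 50% against 37.5%, 90% power, two-sided 5%, cluster size 500, ICC 0.05, 15% loss.
- Design effect: 1 + 499 × 0.05 = 25.95.
- Individuals per arm without clustering: (1.960 + 1.282)² × (0.25 + 0.234375) / 0.125² = 325.7.
- Clinics per arm: 325.7 × 25.95 / 500 = 16.9, so 17. After loss: 17 / 0.85 = 20. The stated figures reproduce.

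**Why omitting township widens intervals.** Between-clinic variance makes up 0.05 × 500 / 25.95 = 0.963 of the variance of a clinic proportion. If townships carry a share s of it, stratification multiplies the true variance of the comparison by about 1 − 0.963s. The unadjusted standard error does not shrink to match.
- s = 0.2: true SE is √0.807 = 0.90 of the estimated one; large-sample type I error 2{1 − Φ(1.96/0.90)}, about 3%.
- s = 0.4: √0.615 = 0.78; type I error about 1%.

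The small-sample downward bias of the sandwich adds back part of the difference, which is why simulation is needed.

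**Simulated type I error at nominal 5%.** Assumptions not in the protocol: 18 townships of 2 clinics and one of 4, and the township shares shown.

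| Analysis | s = 0 | s = 20% | s = 40% |
|---|---|---|---|
| No township, uncorrected sandwich, z | 6.3% | 3.8% | 2.3% |
| No township, small-sample-corrected variance, t on 38 df | about 5% | 3.0% | 1.6% |
| Township strata, clinic level, residual variance, t on 20 df | 4.7-5.0% across shares | | |

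A wider set of runs used shares of 0, 25% and 50%, two layouts (18×2 + 1×4 and 17×2 + 2×3), and cluster-size CV 0 or 0.6. Without township and with an uncorrected z-test it gave 5.7-6.6%, 3.3-3.7% and 1.4-1.7%. With township and t on 20 df it gave 4.3-5.4% throughout.

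**Township indicators with the uncorrected village sandwich.** The model uses 20 of 40 degrees of freedom (19 townships and one treatment term), so squared residuals average about half the true variance. The SE is too small by about √(20/40) = 0.71. The simulated type I error is 17-19%.

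**Power with 20 clinics per arm.** The SE before any stratification gain is √(0.484375 × 25.95 / (500 × 20)) = 0.0355.
- s = 0: 93.0% (t, 38 df) against 91.8% (t, 20 df; critical value 2.09 instead of 2.02). In simulation with cluster-size CV 0.6: 92.0% against 90.1%.
- s = 30%: true SE 0.0355 × √(1 − 0.963 × 0.3) = 0.0299. Unadjusted: Φ((0.125 − 2.02 × 0.0355)/0.0299), about 96%. Stratified, t on 20 df, noncentrality 0.125/0.0299 = 4.18: 97.8% analytically, about 97% in simulation.

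**The case against.** The strongest reply is that the quoted sandwich wording describes only the robustness models. The GEE's variance estimator and covariates are unstated, and a SAP that is not shown may supply a township term and a small-sample correction. This stands in part: nothing in the protocol excludes either. What remains is that the section does fix the models, and for the replication also the clustering level and variance method, yet omits the factor by which clinics were randomised and which the protocol expects to matter.

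Four stronger readings are tempting and are not supported.
- That clustering is handled at the wrong level. The clinic is the randomised unit, so clinic-level clustering is right; township is a stratum, not a missing cluster level.
- That the primary test has an inflated false-positive rate. The excess, to about 6%, appears only when townships barely differ and the variance is uncorrected. If they differ as expected, the test is conservative.
- That the gain from stratification is thrown away. The unadjusted test already rises from about 93% to about 96% at a 30% share; only one to two further points are forgone.
- That the 18% figure describes the protocol. It describes a patch that the protocol does not propose.

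The replication models are not wrong in themselves. They omit township as well, so their agreement with the GEE says nothing on this point.

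**Conclusion.** The point holds as a mismatch between the stratified design and the stated analysis, not as an error in the clustering level or a threat of false positives. Read as written, with an uncorrected sandwich, the nominal 5% test runs at about 6%, 4% or 2% for township shares of 0, 20% or 40%. A small-sample correction without township does not repair this where townships differ; it makes the test more conservative still. The power at stake is small, and every version examined stays at or above the planned 90%.

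The direction follows from the design. The sizes rest on assumed township shares and an assumed spread of clinics over townships, neither of which the protocol gives. A township with a single clinic would contribute no within-township comparison. The change is worth making because it is cheap and makes the inference follow the randomisation; the trial is not invalid without it.

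**What to change.** State in the Data analysis plan that the primary comparison is clustered by clinic and accounts for township, with inference suited to 40 − 19 − 1 = 20 residual degrees of freedom. Two suitable forms are a township-stratified clinic-level analysis with residual variance and t on 20 df, or a within-township permutation test. Recompute the degrees of freedom from the actual clinics per township.

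Derive the reported relative and absolute effects and their intervals from a township-adjusted method as well, so that p-value and interval agree. If GEE is kept for this, its variance needs a correction for the township terms. In the simulations, multiplying the sandwich variance by 40/20 and using t on 20 df gave 4.3-5.4% for the risk difference; the risk ratio was not simulated and should be checked before it is fixed. Do not combine 19 township indicators with an uncorrected village-level sandwich.

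The modified Poisson and linear replication can stay, with the same township adjustment and correction, but should not be relied on to reveal this problem.

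The cost is wording and a little programming. The statistical price is 20 instead of 38 degrees of freedom: one to two points of power if townships do not differ (93.0% to 91.8% with equal clinic sizes, 92.0% to 90.1% with CV 0.6). The 40 clinics still suffice.
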